# Precision medicine phase II study evaluating the efficacy of a double immunotherapy by durvalumab and tremelimumab combined with olaparib in patients with solid cancers and carriers of homologous recombination repair genes mutation in response or stable after olaparib treatment

**DOI:** 10.1186/s12885-020-07253-x

**Published:** 2020-08-10

**Keywords:** PARP inhibitors, Immune checkpoint inhibitors, Olaparib, Durvalumab, Tremelilumab, Homologous repair

## Abstract

**Background:**

Tumors with deficient homologous repair are sensitive to PARP inhibitors such as olaparib which is known to have immunogenic properties. Durvalumab (D) is a human monoclonal antibody (mAb) which inhibits binding of programmed cell death ligand 1 (PD-L1) to its receptor. Tremelimumab (T) is a mAb directed against the cytotoxic T-lymphocyte-associated protein 4 (CTLA-4). This study is designed to evaluate the efficacy of combination of olaparib, durvalumab and tremelimumab in patients with a solid tumors with a mutation in homologous gene repair.

**Methods:**

This phase II study will assess the efficacy and safety of olaparib/D/T association in patients (*n* = 213) with several types of solid cancers (breast cancer, ovarian cancer, pancreatic cancer, endometrial cancer, prostate cancer and others) with at least one mutation in homologous repair genes (*BRCA1, BRCA2, PALB2, ATM, FANCA, FANCB, FANCC, FANCE, FANCF, CHEK2, RAD51, BARD1, MRE11, RAD50, NBS1, HDAC2), LKB1/STK11, INPP4B, STAG2, ERG, CHEK1, BLM, LIG4, ATR, ATRX, CDK12*). Good performance status patients and corresponding to specific inclusion criteria of each cohort will be eligible. STEP1: Patients will receive olaparib 300 mg BID. In absence of progression after 6 weeks of olaparib, they will follow STEP 2 with olaparib and immunotherapy by durvalumab (1500 mg Q4W) + tremelimumab (75 mg IV Q4W) during 4 months and will further pursue durvalumab alone until disease progression, death, intolerable toxicity, or patient/investigator decision to stop (for a maximum duration of 24 months, and 36 months for ovarian cohort). Primary endpoint is safety and efficacy according to progression-free survival (PFS) of olaparib + immunotherapy (durvalumab + tremelimumab) during 4 months followed by durvalumab alone as maintenance in patients with solid cancers and in response or stable, after prior molecular target therapy by olaparib; secondary endpoints include overall survival (OS), disease control rate (DCR), response rate after 6 weeks of olaparib, safety of olaparib/durvalumab/tremelimumab association. Blood, plasma and tumor tissue will be collected for potential prognostic and predictive biomarkers.

**Discussion:**

This study is the first trial to test the combination of olaparib and double immunotherapy based on molecular screening.

**Trial registration:**

NCT04169841, date of registration November 20, 2019

## Background

With the development of cost effective and rapid technology of genome sequencing, precision medicine becomes a new way to think oncology. Current targets involve mainly tyrosine kinases but DNA repair machinery could also be targetable. Some of DNA repair aberrations have been associated with sensitivity to platinum and poly adenosine diphosphate [ADP]–ribose polymerase (PARP) inhibitors like olaparib, suggesting that treatment with a PARP inhibitor (PARPi) may exploit a synthetic lethal interaction, in the presence of alteration of the homologous repair pathway. PARP is involved in multiple aspects of DNA repair, and the PARP inhibitor olaparib has recently been approved for treating ovarian cancers with BRCA1/2 mutations [1, 2]. Similar results were also observed with clinical benefit of olaparib in BRCA2 mutated pancreatic cancer and in BRCA1/2 mutated breast cancer [3, 4]. In addition, a report in the New England Journal of Medicine using a high-throughput, next-generation sequencing assay in prostate cancer showed the detection of genomic alteration in genes involved in homologous repair pathway *BRCA2, ATM, BRCA1, PALB2, CHEK2, FANCA*, and *HDAC2*, is associated with response to olaparib [5]. Recently, TOPAR-B confirmed these results [6]. Thus demonstrating the clinical validation of the usage of precision medicine to position PARP inhibitors like olaparib based on molecular analysis rather than on tumor type.

Similarly, checkpoint inhibitors targeting PD-1 or PD-L1 have demonstrated an efficacy in multiple cancer types. Currently some biomarkers could be used to predict checkpoint inhibitor efficacy in a tumor type agnostic manner. High level of mutation results in high number of neoantigens and antitumor immune response, providing the rational to use immunotherapy to target such tumor types. Microsatellite instability gives rise to a high number of mutations and is associated with good response to immunotherapy whatever the cancer type. A large cohort of patients treated with pembrolizumab in multiple cancer types shows that high tumor mutation burden (TMB) is associated with response, no matter cancer type [7]. Additional DNA damage response (DDR) machinery dysfunction like deficit in homologous repair may lead to accumulation of mutations. After receiving anti-PD-1/PD-L1 treatment, patients with DDR deficiencies had a higher response rate compared to patients without these deficiencies.

Preclinical studies showed DNA damage promotes neoantigen expression [8]. PARPi-mediated catastrophic DNA damage induces accumulated chromosome rearrangements, generates neoantigens and thus increases mutation burden [9]. It is possible that increased DNA damage by PARPi would expand neoantigen expression, leading to greater immune recognition of the tumor. PARPi is also associated with immunomodulation. The PARPi talazoparib increases the number of peritoneal CD8^+^ T cells and natural killer cells and increases production of interferon (IFN)-γ and tumor necrosis factor–α (TNF)- α in a *BRCA1*-mutated ovarian cancer xenograft model [10]. Some preclinical reports also underline the capacity of PARP inhibitors to induce Type I IFN and enhance both MHC and PD-L1 expression. Hence, addition of PARPi to immune checkpoint blockade could complement the clinical benefit of immune checkpoint inhibition. Preclinical data underline a putative synergy and recent data of MEDIOLA study suggest a possible synergy between olaparib and durvalumab [11].

So, we propose to generate a clinical trial based on precision medicine to evaluate the use of immunotherapy in patients with different type of cancers with altered homologous recombination repair genes and without progression after prior targeted therapy.

The objective of this study is to determine whether the combination of olaparib plus durvalumab and tremelimumab could be effective in homologous repair deficient (HRD) tumors.

## Methods

### Study design

This is a multicenter, open label, non-randomized, prospective, phase II study. Patients with mutations in homologous recombination repair genes will be identified through NGS, performed at investigator sites. Analysis will be performed prior to study, as part of a clinical study or in accordance with the usual practice at the investigator site. Study design is depicted in Fig. 1.

**Fig. 1 Fig1:**
[figure not shown]
Study design

### Study objectives

The primary objective of the study is to evaluate the efficacy of olaparib + immunotherapy (durvalumab + tremelimumab) during 4 months, followed by durvalumab alone as maintenance treatment in patients with solid cancers and in response or stable, after prior molecular target therapy by olaparib based on molecular sequencing (mutation in homologous gene repair).

Study secondary objectives are:
To evaluate 6-month disease control rate (DCR) for all cohorts, except ovarian cohort which will be evaluated at 12-months.To evaluate 1 and 2-year PFS and overall survival (OS).To evaluate response rate after 6 weeks of olaparib therapy (STEP 1).To evaluate safety of molecular therapy by olaparib at the end of STEP1.To evaluate safety of molecular therapy (olaparib) + immunotherapy (durvalumab + tremelimumab) and immunotherapy in maintenance (durvalumab alone).

The study exploratory objective is to evaluate the immunogenic effect of olaparib (modification of immune infiltrate and immunogenic cell death markers on biopsy performed before and after olaparib treatment).

### Study endpoints

The primary endpoint is progression free survival (PFS) 6 months after the initiation of immunotherapy for all cohorts, with the exception of ovarian cohort evaluated at 12 months. PFS is defined as the time from the date of first dose of immunotherapy to the date of progression or death from any cause. Progression will be defined using iRECIST criteria.

Secondary endpoints are:
Disease control rate, including stable and responsive disease, evaluated 6 months after immunotherapy initiation for all cohorts except ovarian cohort, evaluated at 12 months.Overall survival (OS) evaluated at 12 and 24 months after immunotherapy initiation defined by the time of the first immunotherapy dose to the date of death from any cause.Response rate evaluated by CT scan, RECIST evaluation after 6 weeks of olaparib therapy.Olaparib toxicity evaluated at the end of STEP1 using CTCAE V5.Olaparib + immunotherapy (tremelimumab + durvalumab) toxicity evaluated at 3, 6 and 12 months after immunotherapy initiation using CTCAE V5.

### Study population and eligibility criteria

Two hundred and seventy patients diagnosed with a solid malignancy, presenting the following histologically confirmed cancers: metastatic breast, lung, prostate, head and neck, endometrial, clear renal cell, pancreatic and urothelial cancer as well as locally advanced or metastatic ovarian cancer. Two hundred and thirteen are expected for STEP 2. Study inclusion and exclusion criteria are detailed in Tables 1 and 2.

**Table 1 Tab1:** General and cohort specific study inclusion criteria

**Inclusion criteria**		
**General step 1**		
1 Patients > 18 years at time of inclusion capable of giving signed informed consent.		
2 Performance status ECOG of 0 or 1.		
3 Life expectancy ≥6 months.		
4 Body weight > 30 kg.		
5 Patients diagnosed with a solid malignancy, histologically confirmed (see cohort specific inclusion criteria below).		
6 Presence of mutation in homologous repair gene (BRCA1, BRCA2, PALB2, ATM, FANCA, FANCB, FANCC, FANCE, FANCF, CHEK2, RAD51, BARD1, MRE11, RAD50, NBS1, HDAC2), LKB1/STK11, INPP4B, STAG2, ERG, CHEK1, BLM, LIG4, ATR, ATRX, CDK12). Homozygote or heterozygote mutations and loss of heterozygosity of the second allele accepted^a^.		
7 At least one lesion measurable as defined by standard imaging criteria for the patient’s tumor type (RECIST v1.1) that can be accurately assessed at baseline and suitable for repeated assessment.		
8 Patients must have normal organ and bone marrow function.		
9 Female and male with adequate contraception method.		
10 For all oral medications patients must be able to comfortably swallow capsules.		
11 Patients affiliated to a social security regimen or beneficiary of the same according to local requirements.		
**General step 2**		
12 CT Scan evaluation after 6 weeks of olaparib should present response or stable disease as defined by RECIST v1.1 criteria.		
**Inclusion criteria**		
**Cohort specific**		
**Breast cancer**^**bd**^ - 2nd line and after	**Lung cancer**^**bd**^ - Non-small cell lung cancer. - Must have progressed after at least a first line with platinum based therapy.	**Head and neck cancer**^**bd**^ - Must have progressed after at least a 1st line with platinum based therapy.
**Metastatic endometrial cancer**^**bd**^ - Progression after one prior systemic, platinum-based chemotherapy.	**Clear cell renal cancer**^**bd**^ - Must have progressed after at least a line with anti-angiogenic agent.	**Pancreatic cancer**^**bd**^ - Must have progressed after at least a line with FOLFIRINOX regimen and/or Gemcitabine based chemotherapy.
**Ovarian cancer**^**ce**^ - Must have received at least one and no more than two lines of prior platinum-containing therapy and progressed after the most recent platinum therapy in a platinum-sensitive timeframe (more than 6 months from the last dose of platinum before randomization).	**Urothelial cancer**^**bd**^ - -2nd line and after.	**Prostate cancer**^**bd**^ - Documented evidence of metastatic castration resistant prostate cancer (mCRPC). - Ongoing therapy with LHRH analog or bilateral orchiectomy. Must have progressed on prior new hormonal agent (enzalutamine or abiraterone) and taxane chemotherapy.

^a^ With patient consent, exome sequencing of tumor and constitutive DNA should have been already performed during prior patient medical care, either as part of a clinical study or in accordance with the usual practice at investigator site, and should comprise the mandatory gene list indicated in inclusion criteria 6

^b^ Metastatic; ^c^ Locally advanced or metastatic; ^d^ ≥2nd treatment line; ^e^ 2nd or 3rd treatment line

**Table 2 Tab2:** Study exclusion criteria

Exclusion criteria	
**Step 1**	
1 Patients involved in GUIDE2REPAIR study planning and/or conduct.	
2 Patients with EGFR, BRAF, ROS1 mutation or ALK rearrangement with lung small cell cancer and are not eligible.	
3 Patient eligible for another study of AstraZeneca Participation in another clinical study with an investigational product within 2 months prior to first olaparib administration.	
4 Administration of any anticancer therapy ≤21 days prior to the first dose of olaparib or 5 times its half-life, whichever smaller.	
5 Any unresolved toxicity NCI CTCAE Grade ≥ 2 from previous anticancer therapy^a^.	
6 Any concurrent chemotherapy, IP, biologic, or hormonal therapy for cancer treatment^b^.	
7 Radiotherapy treatment to more than 30% of the bone marrow or with a wide field of radiation within 4 weeks of the first dose of study drug^c^.	
8 Major surgical procedure within 28 days prior to inclusion and patients must have recovered from any effects of any major surgery IP.	
9 Patients unable to swallow orally administered medication and patients with impairment of gastrointestinal (GI) function or GI disease that may significantly alter drug absorption of oral drugs.	
10 History of allogenic organ, bone marrow or double umbilical cord blood transplantation^d^.	
11 Active or prior documented autoimmune or inflammatory disorders.	
12 Uncontrolled intercurrent illness or patient considered at medical risk due to a serious, uncontrolled medical disorder or psychiatric illness/social situation that would limit study compliance, substantially increase risk of incurring AEs or compromise patient’s ability to give written informed consent.	
13 Currently taking medications with known risk of prolonging the QT interval or inducing “torsades de pointes”.	
14 Concomitant use of known strong or moderate CYP3A inducers.	
15 Resting ECG indicating uncontrolled, potentially reversible cardiac conditions, as judged by the investigator or patients with congenital long QT syndrome.	
16 Patients with myelodysplastic syndrome/acute myeloid leukemia or with features suggestive of MDS/AML.	
17 History of another primary malignancy^e^.	
18 Patient with symptomatic central nervous system (CNS) metastases who are neurologically unstable or require increasing doses of corticosteroids or local CNS-directed therapy to control their CNS disease.	
19 History of active primary immunodeficiency and immunocompromised patients.	
20 Active infection.	
21 Current or prior use of immunosuppressive medication within 14 days before inclusion.	
22 Administration of live attenuated vaccine within 30 days prior to the first dose of IP.	
23 Female patients who are pregnant or breastfeeding or male or female patients of reproductive potential not willing to employ effective birth control.	
24 Known allergy or hypersensitivity to any of the study drugs or excipients.	
25 Prior treatment with any PARP inhibitor including olaparib or immunotherapy.	

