**Step 2**	
Patients should not enter the study if any of the exclusion criteria from STEP 1 and the following criteria for STEP 2 are fulfilled: 26 Patient with progression observed on CT scan performed after 6 weeks of olaparib (STEP 1).	

^a^ Except alopecia, ototoxicity, vitiligo, and laboratory values defined in inclusion criteria. Patients with Grade ≥ 2 neuropathy will be evaluated on a case-by-case basis after consultation with study physician. Patients with irreversible toxicity not reasonably expected to be exacerbated by treatment with olaparib or durvalumab or tremelimumab may be included only after consultation with study physician

^b^ Concurrent use of hormonal therapy for non–cancer-related conditions (e.g., hormone replacement therapy) is acceptable

^c^ Non-palliative radiotherapy within 21 days prior the first dose of study drug or within 6 weeks for therapeutic doses of MIBG or craniospinal irradiation. Palliative radiotherapy (which would be < 30% of the bone marrow) to non-target lesions is allowed

^d^ Patient with allogenic stem cell transplant within 3 months prior the first study dose of Olaparib are not eligible. Patient with myeloablative therapy with autologous hematopoietic stem cell rescue within 8 weeks of the first study drug dose are not eligible. Patients receiving any agent to treat or prevent graft-versus host disease ‘GVHD) post bone marrow transplant are not eligible for this trial

^e^ Except for: malignancy treated with curative intent and with no known active disease ≥5 years before the first dose of IP and of low potential risk for recurrence; adequately treated non-melanoma skin cancer or lentigo maligna without evidence of disease; adequately treated carcinoma in situ without evidence of disease and history of leptomeningeal carcinomatosis

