### Study procedures

All patients respecting all eligibility criteria, namely presenting mutations in homologous repair genes will be included. Regimens sequence is presented in Fig. 1. Study will be divided into two successive steps:
*Step 1*After 6-weeks of olaparib, all patients from STEP 1 will have a CT scan.*Step 2*Depending on CT scan results, two situations will occur:
Patients with stable disease or partial response will follow olaparib + immunotherapy by durvalumab + tremelimumab during 4 months and then continue with durvalumab alone until progression or until 24 dosing maximum of durvalumab for all cohorts except for ovarian cohort with a maximum of 36 dosing.Patient with progression will be withdrawn from the study and treated according to standard care.

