### Statistical analyses

Continuous variables will be summarized using descriptive statistics, i.e. number of subjects with available data (N), mean, median, standard deviation (S.D.), 25–75% quartiles (Q1-Q3) and range. Continuous variables could be transformed as categorical variable using median or using conventional cut-off from bibliography or clinical practice. If required comparison using Chi square (or exact Fisher test) or Student T test (or Wilcoxon Mann and Whitney) tests will be done. Categorical variables will be described by and percentages. The number of missing data will be described.

Each cohort will be described and analyzed separately.

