#### Analysis of safety endpoint(s)

Safety analyses will be performed on the safety-evaluable population, defined as all subjects treated with at least one dose of investigational product.

In each cohort, toxicities and grades will be described according to the type of event at each cycle.

The global following data will also be given:
The number and percentage of patients with at least one adverse event over the study period,The number and percentage of patients with at least one grade 3 or 4 adverse event over the study period,The number and percentage of patients with at least one serious adverse event over the study period,The number and percentage of patients with at least one adverse event leading to treatment premature stop over the study period.

In case a patient experience more than one toxicity, the toxicity with the highest grade will be considered.

Time until grade 3–4 toxicity will be determined using the Kaplan Meier method. Patients without toxicities will be censored.

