#### Analysis of efficacy endpoint(s)

Efficacy analyses will be performed in modified intent-to-treat population (ITT) population ie, all patients with a 6-month evaluation (12-month for ovarian cohort) and at least one dose of durvalumab + tremelimumab. Analyses will be repeated in the per protocol population (patients who had received all the planned doses).

6-month PFS rate (12 month-rate in the ovarian cohort) will be determined using the Kaplan Meier method. 95% Confidence interval (CI) will be provided. Patients alive without progression will be censored.

Median follow-up will be estimated using the reverse Kaplan Meier method.

PFS and Overall survival will be estimated using the Kaplan Meier method. Six-month, 1-year, 2-year rates as well as median OS and PFS will be reported with their 95% CI.

Disease control rates at 6 months will be determined and described with its 95% binomial CI. The same method will be applied to describe the response rate after 6 months of olaparib in each cohort.

All statistical analysis will be performed with SAS 9.4. In case of comparison, tests will be two-sided.

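### As printed, exclusion 6 with footnote b bars prostate-cohort men on an ongoing LHRH analogue, the very therapy that the cohort criterion names as qualifying

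*Protocol article*

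**What the plan says.** Four parts of the protocol article bear on this point.

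- **Table 1, cohort-specific criteria, prostate cancer.** Patients must have documented metastatic castration-resistant disease. The criterion then names the castration route: "Ongoing therapy with LHRH analog or bilateral orchiectomy".
- **Table 2, Step 1, exclusion 6.** This general exclusion covers all cohorts: "Any concurrent chemotherapy, IP, biologic, or hormonal therapy for cancer treatment".
- **Table 2, footnote b.** This is the only exception attached to exclusion 6. It accepts "Concurrent use of hormonal therapy for non–cancer-related conditions" and gives hormone replacement as the example.
- **Table 2, Step 2.** The Step 1 exclusions are applied again at entry to Step 2, together with the added exclusion for progression on the CT scan.

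Study procedures states whom the trial takes: "All patients respecting all eligibility criteria". The article prints no rule that a cohort criterion takes precedence over a general exclusion.

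**The concern.** An LHRH analogue continued in castration-resistant prostate cancer is hormonal therapy for the cancer. Exclusion 6 therefore catches it, and footnote b does not release it. By exempting only non-cancer use, the footnote confirms that use for cancer is barred. The same man is thus named as eligible in one table and excluded in the other.

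What is at stake is eligibility in one cohort. If exclusion 6 is followed as written, men whom the cohort was written to admit fail screening. If the cohort criterion is followed, the same men are enrolled in breach of a printed exclusion and count as eligibility deviations. The repeat of the exclusions at Step 2 adds a second place where this can happen: a man admitted to olaparib could be stopped before the immunotherapy that the primary endpoint concerns.

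**Working it through.** The plan gives no figure on this point, so the check is logical.

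**Rules**

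- Cohort criterion (Table 1): analogue ongoing OR orchiectomy done.
- Exclusion 6 (Table 2): NOT on concurrent hormonal therapy for cancer.
- Footnote b (Table 2): releases only hormonal therapy given for a non-cancer reason.
- Study procedures: all criteria must be met.

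**Cases for a man with metastatic castration-resistant disease**

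1. Analogue, no orchiectomy: meets the cohort criterion, fails exclusion 6.
2. Orchiectomy plus an ongoing analogue: meets the cohort criterion, fails exclusion 6.
3. Orchiectomy, no analogue and no other concurrent hormonal therapy for cancer: satisfies both rules.
4. Neither route: fails the cohort criterion.

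Only case 3 passes both rules.

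**Effect on the analysis sets**

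- Safety-evaluable set: "all subjects treated with at least one dose of investigational product". Exclusion 6 plays no part in the definition.
- Modified ITT set: "all patients with a 6-month evaluation (12-month for ovarian cohort) and at least one dose of durvalumab + tremelimumab". Exclusion 6 plays no part here either.
- Per protocol set: patients given every planned dose. Again there is no reference to exclusion 6.

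So 0 of the 3 definitions depend on exclusion 6. Membership can still change. Take a man in case 1 or 2 who is admitted at Step 1 under the cohort criterion and then checked literally against the Step 1 exclusions at Step 2. He has taken olaparib, so he is in the safety-evaluable set. He would receive no durvalumab + tremelimumab, so he would be in neither the modified ITT set nor the per protocol set. If he is allowed into Step 2, exclusion 6 does not by itself remove him from any set.

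**Counts**

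- Cohorts in Table 1: breast, lung, head and neck, endometrial, renal, pancreatic, ovarian, urothelial, prostate = 9, of which 1 is affected.
- Castration routes in the prostate criterion: analogue, orchiectomy = 2, of which 1 conflicts with exclusion 6.
- Patients: not derivable, because the article gives neither the size of the prostate cohort nor the share of men with orchiectomy.

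**The case against.** The strongest reply is that nobody would be misled. The prostate criterion is specific, exclusion 6 is generic, and reading the specific rule over the general one gives the only sensible result. That stands as to intent: the cohort criterion shows that the analogue is meant to be allowed. It does not make the printed rules agree. Study procedures asks for all criteria to be met, and Table 2 carries footnotes a to e where exceptions were wanted, one of them on hormonal therapy, without this exception.

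A second reply is that the article condenses a full protocol that is not shown. Its tables bear signs of compression, and the exception may sit in the full text. Sites would ordinarily screen from that text, so screen failures or deviations are a possible consequence and not an observed one. This stands, and it limits the point to the printed article. It does not dissolve it, because the issue is a conflict between two statements that are both printed, not an omitted detail.

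A reader might also infer that exclusion 4 is a second error, since it bars "Administration of any anticancer therapy ≤21 days prior to the first dose of olaparib or 5 times its half-life, whichever smaller". The documents do not support that. Whether a given man falls inside that window depends on the agent, the dosing interval and the half-life, and the article gives none of these.

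**Conclusion.** The conflict holds on the printed text. Exclusion 6 with footnote b bars men on an ongoing LHRH analogue from a cohort whose own criterion accepts them, and the repeat of the Step 1 exclusions would, read literally, bar them from Step 2 as well. It is a drafting error that affects 1 of 9 cohorts and 1 of 2 castration routes. Because "Each cohort will be described and analyzed separately", any effect on results stays within the prostate cohort.

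Two stronger inferences should be resisted. One is that the prostate cohort cannot be filled or that the trial loses power. The article gives no figures from which to judge recruitment, and alpha, power and the planned sample size do not depend on this criterion. The other is that an analysis population is defined wrongly. No definition refers to exclusion 6, and membership shifts only if the exclusion is enforced literally. The opposite assurance, that such a man always stays in the efficacy analyses, is not safe either, because of the repeat at Step 2.

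The conclusion assumes only that an analogue continued for castration-resistant disease counts as hormonal therapy for cancer. Severity is low: a change the sponsor could make.

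**What to change.** Add to footnote b of Table 2: *Ongoing LHRH analogue therapy in the prostate cohort is permitted, at Step 1 and at Step 2.* If the full protocol already carries this exception, confirming that is enough.

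A matching exception in exclusion 4 is an optional edit for consistency, not the repair of a demonstrated error.

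The cost is one clause at the next amendment, or two with the optional edit. Design, sample size and analysis do not change.
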